### Target trial design

We will emulate a target trial by conceptualising this non-randomised study as if it were an RCT in clearly defining the eligibility criteria, study population and treatment regimens (table 2).^43 47^ These definitions are informed by ongoing and prematurely closed RCTs comparing the effectiveness of SABR versus surgical resection for early-stage NSCLC.^9 10 15 16 49^ Even after applying the target trial eligibility criteria, it is likely that unobserved confounders (e.g., tumour location) will remain imbalanced between the comparison groups. We will use an instrumental variable (IV) analysis to reduce the risk of bias due to unobserved confounding^44 46 50^ (see the Analyses section for details).

**Table 2 T2:** Overview of the emulated target trial components and their definitions

Protocol component	Emulation protocol
Inclusion criteria	People with first primary NSCLC diagnosis (T1 – T2 N0 M0) between 1 January 2015 and 31 December 2020, according to ICD-10 C34 (all ICD-O-3 morphology codes except those between 8041 and 8045) who received SABR with curative intent or underwent surgical resection within 30 days before or 6 months after diagnosis (base case)
	Aged 18–79 years old if Zubrod performance status 0–2, age 80+if Zubrod performance status 0–1
Exclusion criteria	Synchronous lung cancerPregnancy at time of diagnosis
	Previous thoracic radiotherapy within 5 years prior to diagnosisPrevious metastatic malignancy within 5 years prior to diagnosis
	No surgery or radiotherapyOther types of radiotherapy as index treatment
Treatment strategies	Radiotherapy with curative intent: Stereotactic Ablative Radiotherapy (SABR)Surgical resection: Video-assisted or open thoracic lobectomy+/-mediastinal lymph node dissection (MLND); segmentectomy+/-MLND; wedge resection+/-MLND
Assignment procedure	Two approaches to address confounding: Randomisation will be emulated with an instrumental variable analysis that aims to balance observed and unobserved baseline prognostic measures between the comparison groups (base case analysis). The proposed instrument is the proportion of eligible patients treated with SABR versus surgical resection within the cancer network Randomisation will be emulated via a double robust method- inverse probability of treatment weighting with regression adjustment (alternative analysis)
Time zero	Date of treatment start
Follow-up	Follow-up begins on date of treatment assignment (time zero) and ends 3 years after baseline (base case)
Outcome	Primary outcome: all-cause mortality at 3 years from the date of treatment receipt
	Secondary outcomes: all-cause and lung-cancer mortality at 3 months, 6 months, 12 months, 24 months, and 36 months; time to death; number of days in hospital in 12 months after treatment start; incremental costs; and incremental cost-effectiveness (incremental net health benefits).
Causal contrast of interest	Intention-to-treat effect (patients analysed according to their allocated treatment, regardless of whether they did not fully adhere to treatment or switched to other treatments)

NDRS, National Disease Registration Service; NSCLC, non-small cell lung cancer.

#### Eligibility criteria

A flowchart demonstrating the application of the eligibility criteria to a pilot version of the ‘NDRS linked data’ which included people diagnosed during 2015–2018 is presented in figure 1. The study will include individuals aged 18–79 years old with a recorded Zubrod performance status of 0–2^51^ and those aged 80 years or above with a performance status of 0–1, who were diagnosed with early-stage (T1-2N0M0) NSCLC during 2015–2020 and underwent SABR or surgical resection less than 30 days before or 6 months after diagnosis. We will exclude individuals who had a pregnancy-related HES inpatient or outpatient visit in the 9 months following diagnosis and those who had either synchronous lung cancer or a diagnosis of metastatic cancer in the 5 years before their NSCLC diagnosis or thoracic radiotherapy in the 5 years before their NSCLC diagnosis. We will also consider alternative eligibility criteria as part of the alternative analyses.

**Figure 1 F1:**
[figure not shown]
Flow diagram illustrating the identification of individuals who received SABR with curative intent or surgical resection for T1-2N0M0 NSCLC diagnosed between 1 January 2015 and 31 December 2018 - pilot NRDS data. NSCLC, non-small cell lung cancer; SABR, stereotactic ablative radiotherapy; TNM, tumour, node, metastases.

#### Covariates and time zero

The target trial approach requires baseline covariates to reduce the risk of confounding and to undertake subgroup analyses. From the NDRS Cancer Registry, we will obtain demographic and tumour data including: age at diagnosis, sex, year of diagnosis, tumour histology (adenocarcinoma, squamous, other), tumour stage (T1N0M0, T2N0M0), ethnicity (white, black, South-Asian, other, missing) and income quintile of the Index of Multiple Deprivation.^52^ Zubrod performance status^51^ will be obtained from the Cancer Outcomes and Services Data. From the HES data, we will define comorbidities from inpatient and outpatient visits that include the following diagnoses in the 5 years before the NSCLC diagnosis: myocardial infarction, stroke, heart failure, chronic obstructive pulmonary disease, peripheral vascular disease, diabetes, and interstitial lung disease.

We will define ‘time zero’, which is analogous to the time of randomisation as it is when eligibility criteria are met and follow-up starts, to be the first date that SABR with curative intent is received or surgical resection is undertaken. We will define covariates for ‘seasonality’ by the month either treatment modality was first received, and ‘treatment waiting time’ as the time between the decision to treat and ‘time zero’. We will capture quality of care measures including waiting times and the volume of surgical resections performed in the 12 months before time zero. We will define the cancer alliance and the NHS region within which the surgical hub is located, to account for regional variations.

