#### Treatment strategies

Table 3 shows the SABR regimes considered in this study which follow the Royal College of Radiologists’ guidelines,^6^ practice during the COVID-19 pandemic^41^ and expert inputs from the study’s NSCLC clinical panel. Table 3 also presents the codes used to define surgical resection with curative intent for NSCLC. For both treatment modalities, we will apply a grace period of 30 days before and 6 months after NSCLC diagnosis to account for the prioritisation of diagnosis by pathology as defined by the European Network of Cancer Registries^53^ and to allow for treatment waiting times.

**Table 3 T3:** Overview of the regimens and procedures included within the definition of curative SABR and surgical resection

Treatment definition	Source
54 Gy in 3 fractions over 5–8 days	Clinical Oncology Radiotherapy dose fractionation, Royal College of Radiologists^1^
55 Gy in 5 fractions over 10–14 days	Clinical Oncology Radiotherapy dose fractionation, Royal College of Radiologists^1^
60 Gy in 5 fractions over 10–14 days	Clinical Oncology Radiotherapy dose fractionation, Royal College of Radiologists^2^
60 Gy in 8 fractions over 10–20 days	Clinical Oncology Radiotherapy dose fractionation, Royal College of Radiologists^1^
30–34 Gy in 1 fraction	Faivre-Finn *et al*^3^
60–85 Gy in 5 fractions	Input from clinical panel
50 Gy in 5 fractions	Input from clinical panel
50 Gy in 8 fractions	Input from clinical panel
OPCS-4: E54.3 lobectomy	Input from clinical panel
OPCS-4: E54.4 excision of segment of lung	Input from clinical panel
OPCS-4: E54.5 partial lobectomy of lung NEC	Input from clinical panel

Gy, Gray; NEC, not elsewhere classified; OPCS-4, Office of Population Censuses and Surveys Classification of Interventions and Procedures, version 4; SABR, stereotactic ablative radiotherapy.

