#### Follow-up period and outcomes

The primary outcome is all-cause mortality 3 years from the start of treatment (time zero). We will also report all-cause and lung-cancer specific mortality at 3 months, 6 months, 12 months, 24 months and 36 months as secondary outcomes. We will define lung-cancer attributable mortality as those deaths which include lung cancer (International Classification of Diseases-10: C34) as a cause of death. Multivariable flexible hazard models^54^,^56^ will be fitted to estimate the effect of SABR versus surgical resection on time to death for both all-cause and lung-cancer specific mortality. For these time-to-death analyses, individuals treated during 2015–2023 inclusive will be included to maximise follow-up duration.

The number of days in hospital in the 12 months after the start of treatment will be recorded. We will use information on reasons and route of admission (eg, via emergency room) in the 90 days following the start of treatment to identify admissions attributable to grade three or four adverse events following either treatment modality (see also CEA).

In the pilot NDRS linked registry data, information was available for the primary endpoint (3-year mortality) for each individual in the eligible population. Covariate information was also complete for all the required covariates for the eligible population with the exception of ethnicity, for which the proportions with missing data were low and similar between the comparison groups (1.71% for SABR and 1.34% for surgical resection). The analysis will therefore use observations with complete case information which assumes the missing ethnicity data are independent of the outcome given the covariates included in the analytical models.^57^

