**Figure 3 F3:**
[figure not shown]
Balance of baseline covariates across different levels of the instrumental variable, the proportion within the cancer referral network who received SABR with curative intent versus surgery. 6m, six months prior ;COPD, chronic obstructive pulmonary disorder; HFRS, Hospital Frailty Risk Score; SABR, stereotactic ablative radiotherapy.

The IV approach will report comparative effectiveness and cost-effectiveness across the overall eligible study population. The first stage models will estimate the probability of receiving SABR versus surgical resection given baseline covariates and the IV.^72^ The second stage outcome models will use the general linear models framework and choose the specific model according to whether the endpoint is binary (e.g., mortality at 3 years), continuous (e.g., costs) or time-to-event (e.g., time to death). All estimates will be reported with bootstrapped CIs that make appropriate allowance for clustering.

The IV approach will also report comparative effectiveness and cost-effectiveness according to prespecified subgroups including sex; age group; pre-existing cardiovascular disease or not; hospital frailty score (corresponding to fit, low or intermediate risk); Zubrod performance status (0–2), tumour stage, tumour histology and year of diagnosis.

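### Tumour histology is used as a baseline covariate and subgroup, but it is not tied to tissue taken before time zero and has no untyped level, so its recorded value may depend on the treatment received

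*Protocol article*

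**What the plan says.** Under Covariates and time zero, the protocol article introduces its covariate list with "The target trial approach requires baseline covariates to reduce the risk of confounding and to undertake subgroup analyses". The list includes "tumour histology (adenocarcinoma, squamous, other"), three levels in all. The same sentence gives another variable a level for absent data: "ethnicity (white, black, South-Asian, other, missing"). Time zero is the first SABR date or the date of resection.

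The inclusion row of Table 2 admits ICD-10 C34 tumours with "all ICD-O-3 morphology codes except those between 8041 and 8045". Follow-up period and outcomes reports of the pilot data: "Covariate information was also complete for all the required covariates for the eligible population with the exception of ethnicity". Treatment strategies lets treatment start up to 30 days before the recorded diagnosis, "to account for the prioritisation of diagnosis by pathology as defined by the European Network of Cancer Registries".

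Under Main analyses (base case), "The first stage models will estimate the probability of receiving SABR versus surgical resection given baseline covariates and the IV". The prespecified subgroups there include "tumour stage, tumour histology and year of diagnosis". The same section reports that observed baseline variables were balanced across levels of the instrument in the pilot data (Figure 3, not visible in the text available).

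**The concern.** A baseline covariate has to be fixed by time zero. Read together, these statements do not secure that for histology. An eligible tumour need not carry a specific type, the variable has no level for one that does not, and no value is missing. Unless the flowchart (Figure 1, not visible) removes untyped tumours, they can only be in 'other'. The 30-day window also shows that the pathology which sets the diagnosis can come after treatment.

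Resection provides tissue and SABR does not. A tumour with no informative biopsy could therefore be recorded as adenocarcinoma or squamous after surgery and as 'other' after SABR. Two things are at stake:

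- **Adjusted estimates.** An instrument does not protect against conditioning on a covariate that treatment affects. The doubly robust analysis has the same weakness if it adjusts for histology.
- **The histology subgroup.** Strata defined partly by a consequence of treatment do not hold comparable patients in the two arms, and no instrument repairs that.

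**Working it through.** The article gives no figure for this point, so there is none to reproduce. The check asks what adjustment for recorded histology does to an IV estimate when the true effect is zero and the instrument is valid.

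**Inputs from the article.** SABR share s = 3,000/18,000, about 17%; clinically important difference 7.5 points; surgical 3-year mortality 19.8%.

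**Assumed inputs, not in the article.** Share m of SABR tumours untyped, 10 to 50%; no surgical tumours untyped; true 'other' p = 10% in both arms; mortality of true 'other' relative to the remaining types, δ = +10, 0 or -12 points; mortality gap g from confounding that remains after the other covariates, 3 or 10 points, worse for SABR. Linear two-stage least squares is assumed, with histology (H = 1 if recorded 'other') in both stages; the article states baseline covariates explicitly only for the first stage.

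**Formula.** With D = SABR, Z = instrument and e = the outcome error:

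- bias = -κγ
- κ = Cov(Z,H)/Cov(Z,D), which here equals h1 - h0, with h1 = m + (1 - m)p and h0 = p
- γ = Cov(H,e) / [Var(H) - κ Cov(H,D)]
- Cov(H,D) = s(1 - s)κ
- Cov(H,e) = g Cov(H,D) + δ p (1 - P(H))

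**One case in full: m = 20%, g = 3 points, δ = +10 points.**

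- h1 = 0.20 + 0.80 × 0.10 = 0.28, so κ = 0.18
- Cov(H,D) = 0.17 × 0.83 × 0.18 = 0.0254
- P(H) = 0.17 × 0.28 + 0.83 × 0.10 = 0.1306, so Var(H) = 0.1135
- Cov(H,e) = 0.03 × 0.0254 + 0.10 × 0.10 × 0.8694 = 0.00946
- γ = 0.00946/(0.1135 - 0.18 × 0.0254) = 0.00946/0.1090 = 0.0868
- bias = -0.18 × 0.0868 = -0.0156, or -1.6 points

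With δ = -12 points and all else equal, Cov(H,e) = 0.00076 - 0.01043 = -0.00967 and the bias is +1.6 points. A simulation of 4,000,000 patients gave -1.6 and +1.6.

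**Bias in points (negative favours SABR):**

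| g | δ | m = 10% | 20% | 35% | 50% |
|---|---|---|---|---|---|
| 3 | +10 | -0.8 | -1.6 | -2.7 | -3.9 |
| 3 | 0 | 0.0 | -0.1 | -0.4 | -0.7 |
| 3 | -12 | +0.9 | +1.6 | +2.4 | +3.1 |
| 10 | +10 | -0.9 | -1.9 | -3.5 | -5.6 |
| 10 | 0 | -0.1 | -0.4 | -1.2 | -2.5 |
| 10 | -12 | +0.8 | +1.3 | +1.6 | +1.4 |

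A separate exact large-sample calculation varied other assumptions: 2% of surgical tumours untyped, up to 60% of SABR tumours untyped, weaker confounding of either sign, and squamous tumours 0 or 3 points worse. It gave about -3.5 to +4.5 points. With no histology adjustment, or with true pre-treatment histology, the bias was zero.

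**Would the balance check reveal it?** In that second calculation, with network SABR shares assumed at 5 to 30%, the standardised difference in 'other' between the lowest and highest instrument levels is about 0.04, 0.09, 0.18 and 0.26 at 10, 20, 40 and 60% untyped.

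**Subgroup composition (p = 10%).** At m = 20%, 'other' holds 28% of SABR patients, and 0.20/0.28 = 71% of them are untyped. At 10% untyped the fraction is 0.10/0.19 = 53%; at 50% it is 0.50/0.55 = 91%. In the surgical arm it is zero, or 0.02/0.118 = 17% if 2% of resected tumours are untyped.

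**The case against.** **The premise is inferred.** The article does not say that SABR patients lack a biopsy and gives no untyped share. Its description of SABR as non-invasive concerns the treatment, not the work-up. This stands: the mechanism is possible on the text, not shown. If frail patients go without biopsy, being untyped is also partly a pre-treatment trait, but then it needs its own level and does not belong in 'other'.

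**The reported balance speaks against it.** The bias vanishes when κ = 0, that is, when recorded histology is unrelated to the instrument, and the article reports balance. This stands for the larger shifts, which should have been visible. It is weaker at about 20% untyped, where a standardised difference near 0.09 goes with shifts of about -1.9 to +1.6 points. Figure 3 cannot be inspected for histology, the check covers 2015–2018 only, and balance across the instrument says nothing about the arms within 'other'.

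**The size is modest.** Other covariates absorb part of the confounding, so g may be small. With N = 18,000 and an assumed first-stage partial R² of 0.029, the IV standard error before clustering is √[0.198 × 0.802/(18,000 × 0.029 × 0.17 × 0.83)], about 4.6 points. A shift of 1 to 2 points is less than half of that. This is fair, though bias does not shrink with sample size as the standard error does.

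**It is analysis-plan detail.** Coding rules often are. But the article itself fixes the three levels, the baseline role and the subgroup.

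A reader might infer that the IV estimate is biased in favour of SABR, because 'other' would absorb the worse prognosis of SABR patients. The documents do not support that. The confounding term in Cov(H,e) does push that way when SABR patients are sicker, but the δ term can outweigh it, and the article gives neither quantity.

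**Conclusion.** The point holds as a weakness of definition. As written, the plan can adjust for, and stratify on, a value that treatment helps to determine. The resulting bias in the histology-adjusted IV estimate can take either sign. Across the tabulated assumptions it runs from about -5.6 to +3.1 points against the 7.5-point difference, and the reported pilot balance makes the lower untyped shares, with shifts of roughly 2 points or less, the more credible part of that range. All of this rests on the assumed untyped share, prognosis of true 'other' tumours and residual confounding.

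The subgroup problem is firmer because it depends on neither the sign nor the balance check. Even at 10% of SABR tumours untyped and 10% true 'other', about half of the SABR patients in 'other' would be untyped, set against mostly or wholly typed surgical tumours.

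**What to change.** In Covariates and time zero, define histology from pathology obtained before time zero, and add a level 'not typed before treatment' applied alike in both arms. The extra level helps only with pre-treatment pathology; if specimen typing is allowed in, it will itself be more common after SABR. Report that share by arm and by level of the instrument, and show histology explicitly in the balance check.

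Report the IV and doubly robust estimates with and without histology. If pre-treatment pathology cannot be separated from specimen pathology in the linked data, make the model without histology the base case, and present results by histology descriptively, not as a baseline subgroup.

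The cost is a recode and one additional run of each model, a slight loss of precision where histology is left out, and a histology subgroup that is redefined or becomes descriptive only.

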#### Treatment strategies

Table 3 shows the SABR regimes considered in this study which follow the Royal College of Radiologists’ guidelines,^6^ practice during the COVID-19 pandemic^41^ and expert inputs from the study’s NSCLC clinical panel. Table 3 also presents the codes used to define surgical resection with curative intent for NSCLC. For both treatment modalities, we will apply a grace period of 30 days before and 6 months after NSCLC diagnosis to account for the prioritisation of diagnosis by pathology as defined by the European Network of Cancer Registries^53^ and to allow for treatment waiting times.

**Table 3 T3:** Overview of the regimens and procedures included within the definition of curative SABR and surgical resection

Treatment definition	Source
54 Gy in 3 fractions over 5–8 days	Clinical Oncology Radiotherapy dose fractionation, Royal College of Radiologists^1^
55 Gy in 5 fractions over 10–14 days	Clinical Oncology Radiotherapy dose fractionation, Royal College of Radiologists^1^
60 Gy in 5 fractions over 10–14 days	Clinical Oncology Radiotherapy dose fractionation, Royal College of Radiologists^2^
60 Gy in 8 fractions over 10–20 days	Clinical Oncology Radiotherapy dose fractionation, Royal College of Radiologists^1^
30–34 Gy in 1 fraction	Faivre-Finn *et al*^3^
60–85 Gy in 5 fractions	Input from clinical panel
50 Gy in 5 fractions	Input from clinical panel
50 Gy in 8 fractions	Input from clinical panel
OPCS-4: E54.3 lobectomy	Input from clinical panel
OPCS-4: E54.4 excision of segment of lung	Input from clinical panel
OPCS-4: E54.5 partial lobectomy of lung NEC	Input from clinical panel

Gy, Gray; NEC, not elsewhere classified; OPCS-4, Office of Population Censuses and Surveys Classification of Interventions and Procedures, version 4; SABR, stereotactic ablative radiotherapy.

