#### Outcomes for the CEA

We will calculate the number of life years from the date of treatment start up to 3 years (base case) and for the maximum observation period available (alternative analyses). The NRDS linked data will be used to identify cancer recurrence and disease progression based on diagnoses and procedures captured in subsequent hospital admissions, registration of new tumours and treatment receipt, including surgery, chemo-oncology, immuno-oncology therapy and radiotherapy using a novel approach developed for bowel cancer.^65^ The IV analysis will compare the adjusted proportions of cancer recurrences, common severe adverse events (eg, pneumonia, respiratory distress syndrome or failure and myocardial infarction)^66^ following SABR versus surgical resection. Pending these results, we will apply appropriate HRQoL estimates from the literature.^59^,^61^ For individuals who died of lung cancer, lower HRQoL will be assigned in the six months prior to death.

We will combine survival time with appropriate HRQoL estimates from the literature and use the ‘area under the curve’ approach^67^ to report quality adjusted life years (QALYs) at 3 years from treatment start. We will calculate the incremental net benefit by valuing the incremental QALYs (difference in mean QALYs for SABR vs surgical resection) with alternative threshold levels for cost per QALY gain, including those specified by NICE (eg, £20 000 and £30 000).

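### The comorbidity look-back ends at diagnosis, which may fall up to 30 days after treatment, so post-treatment events can enter as baseline; whether N0 eligibility is also settled after time zero is left open

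*Protocol article*

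**What the plan says.** All references are to the protocol article.

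- **Time zero** (Covariates and time zero): the date of first SABR or of resection. The section likens it to randomisation because "it is when eligibility criteria are met and follow-up starts".
- **Treatment window** (Eligibility criteria): patients qualify if they "underwent SABR or surgical resection less than 30 days before or 6 months after diagnosis". Table 2 has the same base-case window. Treatment strategies applies to both modalities "a grace period of 30 days before and 6 months after NSCLC diagnosis to account for the prioritisation of diagnosis by pathology", and gives waiting times as a further reason.
- **Comorbidities** (Covariates and time zero): taken from HES visits "that include the following diagnoses in the 5 years before the NSCLC diagnosis". The list includes myocardial infarction, stroke and heart failure.
- **Stage** (Table 2; Covariates and time zero): T1-2 N0 M0 is an inclusion criterion and a covariate, taken from the Cancer Registry. The article does not say whether it is clinical or pathological, or whether it is limited to information available before treatment.
- **Adverse events** (Follow-up period and outcomes; Outcomes for the CEA): admissions in the 90 days after treatment start are used to identify severe adverse events, and the cost-effectiveness section compares "common severe adverse events (eg, pneumonia, respiratory distress syndrome or failure and myocardial infarction") between the groups.

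**The concern.** A target trial emulation needs eligibility and baseline covariates to be known at time zero. Here time zero is tied to treatment while the comorbidity window is tied to diagnosis, and diagnosis is allowed to come later. A complication of the operation can then be recorded as a pre-existing condition. It would enter the first-stage treatment model and the weighting and regression of the doubly robust analysis, and it could move the patient into the pre-existing cardiovascular disease subgroup. The same myocardial infarction could count as both covariate and adverse event.

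Stage raises a related but separate question. Only resection yields an operative specimen, with or without nodal dissection. If the registry N category uses that specimen, N0 status in the surgical arm is decided by the treatment. Patients found node-positive would leave that arm, while SABR patients with the same occult disease would stay. A randomised trial analysed by allocation, the contrast Table 2 adopts, would keep them.

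**Working it through.** **1. Does the look-back cross time zero?** Let treatment occur *d* days before the diagnosis date, with *d* up to 30. Time zero is treatment day. The comorbidity window closes at diagnosis, so it includes *d* days after time zero. For *d* > 0 this overlaps the first *d* days of the 90-day adverse-event window. The overlap follows from the stated rules and needs no outside figure.

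**2. Which patients?** The window is written for both modalities. Since it exists partly because pathology takes priority in dating diagnosis, and an operation can itself supply the pathology, patients treated before diagnosis are likely to be mostly surgical. The article does not give their number.

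**3. Does any other rule correct it?**
- Seasonality and treatment waiting time use the treatment date, and surgical volume uses the 12 months before time zero. A time-zero anchor is therefore already in use, but not for comorbidities.
- The alternative analysis that shortens the window from six to three months is not described as removing patients treated before diagnosis.
- Strengths and limitations mentions tumour location, but not the timing of stage or comorbidity.

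**4. Stage, if it draws on the specimen.** The instrument addresses differences that exist before treatment. Removal of upstaged patients would happen after treatment and only in those operated on, so networks that operate more would lose more of them. The instrument is itself a proportion of eligible patients and would be calculated on the selected sample. The doubly robust analysis uses that sample too.

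**5. Illustrative size of the stage effect.** The plan gives no figure for this effect to reproduce. Inputs from Sample size calculations: three-year surgical mortality 19.8% (pilot data) and clinically important difference 7.5 points. Assumptions not in the document: a share *f* = 5-20% of otherwise eligible surgical patients is upstaged, with three-year mortality *m* = 35-45%.

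Understatement = [(1 − *f*) × 19.8% + *f* × *m*] − 19.8% = *f* × (*m* − 19.8%)

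| *f* | *m* = 35% | *m* = 45% |
|---|---|---|
| 5% | 0.05 × 15.2 = 0.76 points | 0.05 × 25.2 = 1.26 points |
| 10% | 1.52 points | 2.52 points |
| 20% | 3.04 points | 5.04 points |

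This range of 0.8 to 5.0 points applies only if every resected patient is staged on the specimen. If only a share *w* treated before diagnosis is affected, multiply by *w*, which is also an assumption:

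- *w* = 5%: 0.04 to 0.25 points
- *w* = 10%: 0.08 to 0.50 points
- *w* = 20%: 0.15 to 1.01 points

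The comorbidity problem cannot be sized: neither the number treated before diagnosis nor the rate of early postoperative events is given.

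**The case against.** The strongest reply is that the certain part is narrow and the rest is inferred. Only some of the seven listed comorbidities are plausible postoperative events. They matter only if recorded between treatment and a diagnosis date at most 30 days later, and any deaths they cause still count in all-cause mortality from time zero. This limits the effect but does not remove the contradiction.

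On stage, four stronger conclusions are tempting, and the document does not support them.

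- *That surgical stage is read from the specimen.* The pathology wording explains the treatment window and the dating of diagnosis. It says nothing about the source of T and N, a definition that an article may leave to a fuller document.
- *That the 30-day window causes the stage problem.* If registry stage is pathological, every resected patient is exposed, whatever the diagnosis date. The 0.8-5.0 point range belongs to that broad case and should not be attributed to the window.
- *That the net bias favours surgery.* That is the expected direction for loss of upstaged patients and for adjusting for postoperative events. An opposite effect is possible: Table 2 does not require pathological confirmation, so the SABR arm could contain lower-risk lesions that a specimen would have excluded.
- *That all covariates are anchored to diagnosis.* Seasonality, waiting time and surgical volume are not, and no look-back is stated for frailty or performance status.

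**Conclusion.** The point holds in two parts of unequal certainty.

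First, from the text alone: the stated comorbidity look-back runs past time zero for anyone treated before diagnosis, against the article's own definition of time zero, and no other rule corrects it. The number affected is unknown and the effect may be small.

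Second, conditionally: if registry T and N use the resected specimen, N0 eligibility in the surgical arm is decided after time zero for any resected patient, and the instrumental variable would not remove the resulting selection. The understatement of surgical mortality would be 0.8-5.0 points on the assumed upstaging and mortality if all resected patients are affected, and a fraction of that if only those treated before diagnosis are. The upper end is a large part of the 7.5-point difference of interest, but neither a size nor a net direction can be established from the document.

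**What to change.** 1. End the comorbidity look-back, and any other HES-based baseline look-back such as one for frailty, on the day before the index treatment or its admission. This is needed whatever the source of stage.
2. Add a sensitivity analysis excluding patients whose time zero precedes their diagnosis date, and report how many there are in each arm.
3. State whether registry T and N are clinical or pathological. Use pre-treatment clinical T and N for eligibility in both arms where the registry holds them, keeping patients upstaged at resection in the surgical arm, with a sensitivity analysis where they are not held.

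Step 2 does not replace step 3: surgical patients diagnosed before the operation could still carry a pathological stage.

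Cost: steps 1 and 2 need re-derivation of covariates from linked data already planned for the study. Step 3 is less certain. The article does not show that pre-treatment stage is available, some patients will lack it, and restoring upstaged patients may need registry records outside the T1-2N0M0 population that the Data section identifies.
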